## Methods/design

### Objective

The primary objective of this study is to prospectively evaluate that the pathological response rate after 2 cycles of CAPOX is not inferior to that of 4 cycles in patients with low-risk and intermediate-risk stage II/III rectal cancer, which may provide evidence for the feasibility of early identification of chemotherapy-insensitive population.

The secondary objectives are as follows: (1) to explore the difference in clinical remission rate between 2 and 4 cycles of CAPOX in patients with low-risk and intermediate-risk stage II/III rectal cancer; (2) to explore the effectiveness/ineffectiveness of NCT at early cycles (after 2 cycles of CAPOX) in predicting the long-term prognosis (3 years overall survival (OS)/disease-free survival (DFS)); (3) to confirm the perioperative safety of NCT alone; (4) to construct a model using 2-cycle imaging indicator to predict a 4-cycle pathological remission; and (5) to explore the feasibility of artificial intelligence (AI)-assisted imaging indicators to predict pTRG after NCT.

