**Fig. 1 Fig1:**
[figure not shown]
Flow diagram

Low- and intermediate-risk stage II/III rectal cancer was defined as (1) middle and low rectal cancer (below the peritoneal reflection): T3a-bN0-1M0, EMVI ( ±), MRF (-) (≥ 2 mm) and middle and high rectal cancer (above the peritoneal reflection): T3a-c/T4aN0-1M0, EMVI ( ±), MRF (-) (≥ 2 mm); (2) mesorectal lymph node with short diameter ≥ 8 mm or highly suspected metastasis not more than 3; and (3) the short diameter of the lateral lymph node ≤ 7 mm. Inclusion, exclusion, and withdrawal criteria have been detailed in Table 1. The screening process is set to be performed by experienced surgeons at each center. Enrolled patients are allowed to quit at any time without any reason or responsibility.

**Table 1 Tab1:** Details of the inclusion, exclusion, and withdrawal criteria

Inclusion criteria	
1)	Patients aged between 18 and 75 of either sex
2)	Patients with low- and intermediate-risk stage II/III rectal cancer evaluated by MRI and TRUS: middle and low rectal cancer (below the peritoneal reflex line): T3a-bN0-1M0, EMVI ( ±), MRF (-) (≥ 2 mm) and middle and high rectal cancer (above the peritoneal turning line): T3a-c/T4aN0-1M0, EMVI ( ±), MRF (-) (≥ 2 mm) Mesangial lymph node with short diameter ≥ 8 mm or highly suspected metastasis no more than 3 The short diameter of the lateral lymph node ≤ 7 mm Patients with ultra-low rectal cancer who match the above criteria and can achieve negative circumferential resection margin under extralevator abdominoperineal excision (ELAPE) surgery will be included in the group
3)	In colonoscopy or anal examination, the lower boundary of the lesion is ≤ 12 cm from the anal verge
4)	Patients with no distant metastasis (including suspected lung nodule metastasis) confirmed by chest and abdomen CT examination; no extra-regional lymph node metastasis (≥ 10 mm)
5)	Pathologically diagnosed rectal adenocarcinoma
6)	Eastern Cooperative Oncology Group (ECOG) score: 0–1
7)	Patients with primary rectal cancer who have not received surgery (except palliative ostomy), radiotherapy, systemic chemotherapy, or other anti-tumor treatments before enrollment

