### Randomization and intervention

Each sub-center will be responsible for potential enrollment and consent-taking. Central randomization will be performed as soon as the enrollment is determined using the central automated randomization system offered by the O-trial online system (https://plus.o-trial.com/). Sub-center will upload the information of eligible patients on the O-trial system, which will sequentially number and randomize the uploaded patients into 2 or 4 cycles of CAPOX in a 1:1 ratio automatically. No stratification is included in the current study.

Patents in both groups will undergo TME surgery after 2 or 4 of CAPOX. Each cycle of CAPOX includes oxaliplatin 130 mg/m^2^, once daily on day 1, every 21 days and capecitabine 1000 mg/m^2^, twice daily on days 1 to 14, every 21 days. TME surgery was performed by experienced colorectal surgeons 2–3 weeks after the last cycle of preoperative CAPOX.

Postoperative adjuvant treatment will be performed according to the ESMO and Chinese guidelines for colorectal cancer [19, 20]. Based on the pathological stage, patients with a positive CRM or N2 stage would be recommended to undergo postoperative radiotherapy. Adjuvant chemotherapy was recommended for N + patients. The long-term survival of the patients will be followed up.

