### Endpoints

The primary endpoint is the proportion of patients with pTRG3, which is determined postoperatively by each sub-center and verified by the primary center.

The secondary endpoints include (1) the proportion of patients with TRG on MRI (mrTRG) (1–5) after 2 cycles/4 cycles of CAPOX; (2) the proportion of patients with pTRG (0–2); (3) survival prognosis of patients with different pTRG, containing disease-free survival (DFS), local recurrence rate (LR), distant recurrence rate (DR), and overall survival (OS); (4) 3-year DFS and OS of patients with different pTRG; (5) the predicted imaging indicators of pTRG; (6) the accuracy of pTRG judged by imaging; (7) the adverse effects of chemotherapy; (8) the incidence of perioperative complications; and (9) the QOL of patients during chemotherapy and after surgery.

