### Data-analysis

The trial statistician, who will be blinded to randomization, will carry out the data analysis process. Before analysis, they will assess the integrity of collected data, and repeated or missing data will be described accordingly. Demographics and repeatedly measured clinical characteristics of participants will be summarized as the baseline.

SPSS for Windows, version 25 (IBM Corp, Armonk, NY), and GraphPad Prism for Windows, version 8.0.0 (GraphPad Software, San Diego, California), are used for data analysis. Continuous data are shown as the mean and standard deviation. Categorical variables are represented as percentages. Continuous variables are compared using the Mann–Whitney *U* test. Categorical variables are compared between groups using Fisher’s exact test or the chi-square test. Fisher’s exact test or the chi-square test is used to compare the proportions of patients with pTRG3, the proportion of patients with TRG on MRI (mrTRG) (1–5) after 2 cycles/4 cycles of CAPOX, and the proportion of patients with pTRG (0–2). Survival of patients (OS, DFS) is compared using Kaplan–Meier analysis. Statistical significance is defined as a *p*-value less than 0.05. Especially, in the 4 cycles of the CAPOX group, patients who receive less than 3 cycles of chemotherapy due to adverse effects or drop-out will be analyzed as the 2 cycles of the CAPOX group; others will be analyzed in the 4 cycles of the CAPOX group analysis.

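### The one survival comparison named is unadjusted, so it can describe outcome by pTRG but cannot show that response predicts prognosis beyond screening stage (minor)

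*Protocol article*

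**What the plan says.** In the Protocol article, Endpoints section, secondary endpoint 3 is prognosis (DFS, local and distant recurrence, OS) by pTRG category, and endpoint 4 is "3-year DFS and OS of patients with different pTRG". Neither separates the two arms. Under Objective, the second secondary aim is "to explore the effectiveness/ineffectiveness of NCT at early cycles (after 2 cycles of CAPOX) in predicting the long-term prognosis", measured by 3-year OS and DFS.

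The Data-analysis section gives one sentence on method: "Survival of patients (OS, DFS) is compared using Kaplan–Meier analysis". It names no groups, covariates or regression model, and the next sentence sets the significance threshold at p < 0.05. Because the survival endpoints are defined by pTRG, that sentence has to cover the pTRG comparison.

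Three other statements bear on how comparable the groups are:

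- **Eligibility admits a range of stage.** Below the peritoneal reflection it is T3a-b with N0-1. Above it, it is "T3a-c/T4aN0-1M0, EMVI ( ±), MRF (-) (≥ 2 mm").
- **Adjuvant treatment follows pathology.** The section Randomization and intervention says that "patients with a positive CRM or N2 stage would be recommended to undergo postoperative radiotherapy", and "Adjuvant chemotherapy was recommended for N + patients".
- **Randomisation was simple.** "No stratification is included in the current study".

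**The concern.** pTRG is observed after treatment and surgery, so patients with pTRG3 and pTRG 0–2 are not exchangeable. If higher cT substage, nodal involvement or EMVI at screening makes both poor regression and recurrence more likely, the two curves will separate even when regression itself adds nothing.

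This matters because of the use the trial has in mind. The Discussion looks ahead to screening out poor responders for other treatment. Those patients already have an MRI and TRUS stage before any chemotherapy, so the useful question is what response adds to it. A Kaplan–Meier comparison at p < 0.05 does not answer that, and a small p-value could easily be read as if it did.

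**Working it through.** **The plan's own figure.** The article gives no event rate, hazard ratio or power for the pTRG survival comparison, so there is nothing to reproduce. What it does give is the number of evaluable patients, 2 × 249 = 498, and a pTRG3 rate of 27.9% after 4 cycles (Sample size calculation).

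**Assumed inputs, not in the documents.** 3-year DFS of 80%; the prevalence of the baseline factors; the strength of their link with pTRG3 (odds ratio) and with DFS (hazard ratio h). The true pTRG effect given the baseline factors is set to none.

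**Step 1: one stage factor, closed form.** Let half the patients have the higher stage, with odds ratio 3 between higher stage and pTRG3. If x is the pTRG3 risk at lower stage, the overall rate of 27.9% requires

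x + 3x/(1 + 2x) = 2 × 0.279 = 0.558,

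which gives x = 0.173, and 0.385 at higher stage. The share with higher stage is then

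- among pTRG3: 0.385/0.558 = 0.690
- among pTRG 0–2: (1 − 0.385)/(2 − 0.558) = 0.426

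The early hazard ratio between pTRG groups, due to stage alone, is

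[1 + 0.690(h − 1)] / [1 + 0.426(h − 1)].

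- h = 1.5: 1.345/1.213 = 1.11
- h = 2: 1.690/1.426 = 1.19
- h = 3: 2.380/1.852 = 1.29

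**Step 2: one stage factor, simulation** (498 patients, 1,500 runs per setting, two-sided 0.05).

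| Stage–pTRG3 odds ratio | Stage h = 1.5 | h = 2 | h = 3 |
|---|---|---|---|
| 1 | HR 1.00, rejects 5% | 1.00, 5% | 1.00, 4% |
| 1.5 | 1.04, 5% | 1.07, 8% | 1.11, 8% |
| 2 | 1.08, 7% | 1.13, 8% | 1.21, 16% |
| 3 | 1.10, 8% | 1.19, 13% | 1.32, 23% |

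Stratifying the log-rank test by stage brings rejection back to 4–6% in every cell. The bottom row agrees with the closed form to within 0.03.

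**Step 3: three factors** (prevalence 50%, 25% and 25%), each acting equally on the odds of pTRG3 and on the hazard.

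| Effect of each factor | Unadjusted HR | Unadjusted rejection | Adjusted Cox rejection |
|---|---|---|---|
| 1.5 | 1.10–1.12 | 8–9% | about 5% |
| 2 | 1.34–1.36 | 30–34% | 5–6% |

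The ranges cover separate simulation runs. The adjusted hazard ratio was 0.99–1.00 throughout.

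**Step 4: adjuvant treatment.** It is recommended on pathological N stage and margin. Suppose it goes to the higher-stage patients and works (assumed hazard ratio 0.7). At odds ratio 3, the unadjusted hazard ratios fall from 1.10/1.19/1.32 to 1.02/1.10/1.21, and rejection from 8/13/23% to 5/7/15%. In this setting it pulls the curves together.

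**Step 5: randomised arm.** The Sample size calculation expects pTRG3 to rise by no more than 10% with 2 cycles. At the limit, read as percentage points (27.9% against 37.9%), the arm–pTRG3 odds ratio is (0.379/0.621)/(0.279/0.721) = 1.58. Read as a relative rise (to 30.7%), it is 1.14. Under the first reading the 2-cycle arm supplies 0.379/0.658 = 0.576 of pTRG3 and 0.621/1.342 = 0.463 of pTRG 0–2. Even an assumed arm hazard ratio of 1.5 then gives only (1 + 0.576 × 0.5)/(1 + 0.463 × 0.5) = 1.288/1.231 = 1.05. Arm belongs in the model but is unlikely to be the main source of distortion.

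**The case against.** The strongest reply is that the endpoints are descriptive. Survival by regression grade is a legitimate result, a marker can be prognostic without being independent of stage, and the article nowhere claims that pTRG is independent. On that reading, an unadjusted difference is not a false positive. This stands for endpoints 3 and 4 taken alone. It does not carry over to objective 2, whose value lies in what response adds to known stage.

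Second, the article does not exclude a regression model, and the full protocol or SAP may contain one. That also stands in part. Missing covariate lists or intervals are no fault in an article. The point is that the one comparison it does name, tied to a significance threshold, does not suit the predictive question.

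Two stronger readings are tempting but not supported:

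- **That the pTRG groups do differ in baseline stage.** No section reports stage by pTRG, and eligibility narrows the range (N0-1, MRF negative, T3a-b below the reflection). With no association, the error rate stays near 5%.
- **That adjuvant treatment makes pTRG look prognostic.** It is not assigned by pTRG, and if effective it can shrink the apparent effect, as step 4 shows.

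Finally, pTRG is known only after resection, so it cannot itself redirect patients before surgery. The imaging endpoints serve that purpose.

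**Conclusion.** The point holds in a limited form. The named comparison describes survival by pTRG but cannot support a statement that response predicts prognosis beyond the screening assessment. With no true pTRG effect, the apparent hazard ratio is about 1.0 to 1.35 and the false-positive rate about 5% to 30%. The upper end needs three baseline factors that each double both the odds of pTRG3 and the hazard; a single factor gives at most 23% in the settings tried. All of this rests on assumed DFS, prevalences and effect sizes, and it vanishes if stage and pTRG are unrelated.

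The endpoints are secondary and partly exploratory, and the primary conclusion on pTRG3 is not affected. Severity is minor.

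**What to change.** Keep the Kaplan–Meier curves by pTRG and label them descriptive. Make the stated comparison a Cox model for DFS and for OS, with time counted from surgery because pTRG is defined only then. Compare pTRG3 with 0–2, adjust for screening cT substage, cN, EMVI, tumour location and randomised arm, and report the hazard ratio with its 95% CI. If OS events are sparse, use fewer covariates, chosen in advance. Tabulate adjuvant chemotherapy and radiotherapy by pTRG group beside the result, so that readers can judge their possible influence.

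The cost is a few sentences of SAP text and one model per endpoint. Stage and location are needed to decide eligibility, so they are on file. EMVI is admitted either way, so check that its status is recorded for every patient. The downside is that the adjusted association may be weaker or less precise than the raw curves suggest. If an existing SAP already specifies such a model, one sentence saying so settles the matter.

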8)	The main organ function is normal and meets the following standards: (1) blood routine criteria: HB ≥ 9 g/dL, WBC ≥ 3.5/4.0 × 10^9^/L, neutrophil ≥ 1.5 × 10^9^/L, PLT ≥ 100 × 10^9^/L; (2) blood biochemical criteria: Crea and BIL ≤ 1.0 times the upper limit of normal value (ULN), ALT and AST ≤ 2.5 times the upper limit of normal value (ULN), alkaline phosphatase (ALP) ≤ 2.5 × UNL, total bilirubin (Tbil) ≤ 1.5 × UNL
9)	No history of 5-Fu and platinum drug allergy
10)	Females of childbearing age must undergo a pregnancy test (serum or urine) 7 days before enrollment with a negative result and are willing to use appropriate contraceptive methods during the trial and 8 weeks after the last administration
11)	Patients voluntarily join the study and sign informed consent forms with good compliance and follow-up
Exclusion criteria joined	
1)	Patients considering lynch syndrome
2)	Patients who do not consider metastasis in the initial diagnosis but proved to be distant metastases during the treatment
3)	Previously or concurrently suffering from other malignant tumors (including concurrent colon cancer), except for cured skin basal cell carcinoma and cervical carcinoma in situ
4)	Pregnant or nursing women
5)	Lateral lymph nodes ≥ 7 mm
6)	Patients with severe cardiovascular disease and diabetes difficult to control
7)	Patients with mental disorders
8)	Patients with severe infection
9)	Patients undergoing thrombolysis/anticoagulation therapy with bleeding diathesis or coagulation dysfunction, or suffering aneurysm, stroke, transient ischemic attack in the past year
10)	Patients with a history of kidney disease, urinary protein, or clinically abnormal renal function
11)	Patients with a history of gastrointestinal fistula, perforation, bleeding, or severe ulcer
12)	Patients with severe gastrointestinal diseases that affect the absorption of oral chemotherapy drugs
13)	Patients participating in another clinical trial within 4 weeks before treatment
14)	Patients pathologically diagnosed with mucinous component or the signet-ring cell carcinoma
Withdrawal criteria	
1)	Patients refusing further treatment
2)	Patients having severe adverse reactions to chemotherapy and being unable to complete 2 cycles of chemotherapy

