### Sample size calculation

According to phase II trial [16], the proportion of patients who had poor pathological remission (pTRG 3) after 4 cycles of CAPOX was 27.9%. The proportion of pTRG3 after 2 cycles of CAPOX is expected to increase by no more than 10%. The non-inferiority test is used with *α* = 0.05, (1-β) = 0.8, and the non-inferiority margin (hazard ratio) value δ is set as 0.05. Pearson chi-square test is used to calculate the sample size required for the experiment, and 249 samples are required for each group calculated by a normal approximation algorithm [25]. Ten percent of patients are estimated to withdraw from the group or lost to follow-up; 277 patients are needed in each group. The planned enrollment time is 2.5 years, and the total number of patients is about 554 cases. Meanwhile, it is assumed that the dropout rate of patients in the 4 cycles of the CAPOX group is about 6% due to intolerance of chemotherapy. Therefore, it is estimated that 294 patients would be included in the 2 cycles of the CAPOX group and 260 patients in the 4 cycles of the CAPOX group.

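### Analysing 4-cycle patients with fewer than 3 cycles in the 2-cycle group breaks the randomised comparison of pTRG3 and biases it in an unknown direction

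*Protocol article*

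**What the plan says.** The Randomization and intervention section allocates centrally; the system will "randomize the uploaded patients into 2 or 4 cycles of CAPOX in a 1:1 ratio automatically". The Endpoints section states: "The primary endpoint is the proportion of patients with pTRG3", where a higher proportion is worse.

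The Data-analysis section then redefines the groups. Within the 4-cycle arm, "patients who receive less than 3 cycles of chemotherapy due to adverse effects or drop-out will be analyzed as the 2 cycles" group, while "others will be analyzed in the 4 cycles of the CAPOX group analysis". Nothing comparable is stated for patients randomised to 2 cycles, and no analysis of pTRG3 by allocated arm is described.

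The Sample size calculation section builds the rule in. It starts from 277 per group, assumes about 6% intolerance in the 4-cycle arm, and expects that "294 patients would be included in the 2 cycles of the CAPOX group and 260 patients in the 4 cycles".

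The withdrawal criteria in Table 1 cover part of the same ground: "Patients having severe adverse reactions to chemotherapy and being unable to complete 2 cycles of chemotherapy".

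**The concern.** Randomisation makes the two groups comparable only if patients are analysed where they were allocated. Here toxicity or drop-out, both of which occur after allocation, decides the group for the primary endpoint. The rule works in one direction and on one arm only.

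The selection may also be linked to response. Both arms are re-imaged after 2 cycles, and the Monitoring and reporting section lists tumour progression among the adverse events and advises patients with progressive disease to withdraw. A 4-cycle patient who progresses at that point could therefore be counted against the 2-cycle arm. The opposite selection is equally conceivable.

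The non-inferiority conclusion then rests partly on how a self-selected subgroup responds. The rule is not limited to pTRG3, so it would also carry patients who stopped 4-cycle treatment for toxicity into the 2-cycle column of the chemotherapy adverse-effects endpoint.

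**Working it through.** **1. Reproduce the plan's figures.** The inputs, all from the Sample size calculation section, are a 4-cycle pTRG3 rate of 27.9%, an allowed increase of 10 percentage points, α = 0.05 and power 0.80. The section labels the margin a hazard ratio of 0.05 and gives no sidedness, so I tried the possible readings with

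n = 2p(1−p)(z₁₋α + z₁₋β)² / margin²

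- Margin 0.10, one-sided 0.05: 2 × 0.279 × 0.721 × (1.645 + 0.842)² / 0.10² = 248.7, so **249**, as stated.
- Margin 0.10, one-sided 0.025: 316.
- Margin 0.05, one-sided 0.05: 995.

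The first reading is used below. It is inferred from 249 and is not stated. 249 / 0.90 = 276.7, so 277. 0.06 × 277 = 16.6, so about 17 are moved: 277 + 17 = 294 and 277 − 17 = 260. The two unequal figures are therefore exactly the planned transfer.

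**2. Effect of the move on the compared rates.** Let p₂ and p₄ be the true rates in the randomised arms and r the rate in the 17 moved patients. The documents give no r, so it is varied.

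- Analysed 4-cycle rate = (277 p₄ − 17 r) / 260
- Analysed 2-cycle rate = (277 p₂ + 17 r) / 294

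Example with p₄ = 0.279, p₂ = 0.379 and r = 0.10: (77.3 − 1.7) / 260 = 0.291 and (105.0 + 1.7) / 294 = 0.363. A true 10-point deficit appears as 7.2 points.

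Example with equal arms at 0.279 and r = 0.50: (77.3 − 8.5) / 260 = 0.265 and (77.3 + 8.5) / 294 = 0.292. A spurious deficit of 2.7 points appears.

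**3. Error rates.** The test is an unpooled Wald non-inferiority test against 10 points at one-sided 5%, with all 277 per arm evaluable. Results are simulated and agree with a normal approximation.

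| r in moved patients | Apparent difference when the truth is 10 points | False non-inferiority | Power when arms are equal |
|---|---|---|---|
| 0 | 6.0 | 0.26 | 0.97 |
| 10% | 7.2 | 0.17 | 0.94 |
| 27.9% | 9.4 | 0.07 | 0.84 |
| 37.9% | 10.6 | 0.035 | 0.74 |
| 50% | 12.1 | 0.014 | 0.60 |
| As randomised, any r | 10.0 | 0.05 | 0.84 |

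False non-inferiority exceeds 0.05 when r is below about 32.5% and falls under it when r is above that. With 249 evaluable per arm instead of 277, the false non-inferiority column reads 0.24, 0.16, 0.065, 0.036 and 0.015, so the pattern does not depend on full evaluability.

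**4. Overlap with Table 1.** Fewer than 3 cycles includes 0 or 1. A 4-cycle patient who stops after 1 cycle because of a severe reaction meets the withdrawal criterion and also the rule that analyses such patients with the 2-cycle group.

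**The case against.** The best defence is that the rule is open, expected to touch only 6% of one arm, and groups patients by what they received, which suits a question about response after 2 or 4 cycles. If the moved patients respond as the 2-cycle arm does at the margin (37.9%), the rule is conservative, with false non-inferiority of about 0.035. The openness is real, and the article does not conceal the intolerance. But a conservative outcome in one scenario is not error control, and the cost there is power (0.74 instead of 0.84).

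A reader might go further than the documents allow in three ways.

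- **That the rule more than triples false non-inferiority.** At 6% moved this needs r below about 13%, less than half of the 27.9% in their own arm. The documents give no such rate. It could arise if moved patients without a pTRG result stayed in the denominator as not pTRG3 (r near 0), but the article does not say how they are counted.
- **That 294 and 260 contradict 1:1 allocation.** They are expected analysed sizes derived from 277 per arm. Allocation stays 1:1.
- **That the analyst cannot be blinded.** The article refers to "The trial statistician, who will be blinded to randomization". Someone else could apply the rule and hand over coded groups.

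The overlap with Table 1 is an ambiguity, not proof of bias. The two texts could be read in sequence, with withdrawal first and then regrouping of those with exactly 2 cycles. The article does not say so.

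Finally, the Data-analysis section names only a chi-square or Fisher test at p < 0.05, so any false non-inferiority rate presupposes the margin test implied by the sample size section.

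**Conclusion.** The rule is wrong as written and should be changed before analysis. It is a stated rule for the primary comparison, not a detail left to an analysis plan that is not shown. It makes group membership depend on a post-randomisation event in one arm.

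The supportable claim is loss of error control with bias of unknown direction: false non-inferiority between about 0.014 and 0.26, and power between about 0.60 and 0.97, as r goes from 50% to 0. If the moved patients are typical of their own arm, the effect is small (0.07 against 0.05).

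These figures rest on four assumptions: the inferred 10-point, one-sided 5% test; 17 of 277 moved; all 277 per arm evaluable; and r, which is unknown. The breach of the randomised comparison rests on none of them.

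**What to change.** - Make the primary pTRG3 analysis as randomised, with every patient in the allocated arm whatever the number of cycles received.
- Prespecify the handling of patients without a resected specimen or pTRG result, since the endpoint needs a specimen and 10% loss is expected. For example, analyse all randomised patients with a pTRG result, with sensitivity analyses that count missing as pTRG3 and that use multiple imputation.
- Add a supportive per-protocol analysis that excludes non-adherent patients and does not transfer them. State that it too selects after randomisation: with r = 10% and a true 10-point deficit, excluding the 17 gives 0.379 − 0.291 = 8.8 points and about 9% false non-inferiority.
- Keep grouping by cycles received as exploratory only, and remove 294 and 260 as the analysis group sizes.
- Reconcile the Table 1 withdrawal criterion with the Data-analysis rule for patients who complete fewer than 2 cycles.

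The cost is wording in the protocol and analysis plan, with no extra patients. The downside is slight dilution. If 6% of the 4-cycle arm respond as 2-cycle patients with no selection, that arm shows 0.94 × 27.9% + 0.06 × 37.9% = 28.5%, and the contrast is 37.9 − 28.5 = 9.4 points instead of 10. Judged against the effect of cycles received, false non-inferiority is then about 7%. The per-protocol analysis is there to show this.
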